#### Resting-state fNIRS

2.7.6

A near-infrared quantitative brain function imaging device (model: The NirScan-6000A, manufactured by The Danyang Huichuang Medical Equipment Co., Ltd.) will be used to measure changes in hemoglobin (Hb) concentration at rest. This device non-invasively monitors oxygenated hemoglobin (HbO2), deoxygenated hemoglobin (HbR), and total hemoglobin (HbT) by analysing changes in light intensity. It is equipped with 24 source transmitters and 24 receivers, allowing for up to 48 measurement channels. These channels cover six brain regions on each side: the frontal, parietal, and occipital lobes. The left premotor cortex, right premotor cortex, left prefrontal cortex, right prefrontal cortex, left parietal lobe, right parietal lobe, left occipital lobe, and right occipital lobe were selected as the regions of interest (ROIs). Near-infrared light at three wavelengths (730, 808, and 850 nm) is emitted by each source, and detected by nearby receivers after passing through the brain’s cortex. Using the Beer-Lambert Law, the device calculates Hb concentration changes by assessing near-infrared light absorption in each channel (33).

All fNIRS brain function tests will be conducted in a quiet environment free from noise and other distractions in a designated testing room. During the resting phase, the child will be required to sit upright, maintain a state of mental relaxation, and keep their head as motionless as possible. During measurement, participants will wear a cap on their heads, adjust the probe, and conduct the test, which involves switching on all channels to measure changes in blood and oxygen signals of the cerebral cortex in the resting state as well as recording the spontaneous brain activity of the subject.

### Interventions

2.8

#### Behavioral training based on VR technology

2.8.1

The intervention group will participate in 12 weeks of behavioral training targeted to preschool-aged children with ASD based on VR technology developed by the researchers. This training will be conducted twice a week for one hour. The same therapist will accompany each child during each intervention session. A comprehensive course schedule is provided in **Supplementary Table 1**.

The intervention will use nonwearable VR technology, including a desktop computer (Lenovo) with an integrated LED interactive floor screen (3m*3m), and a resolution of P3.91. The nonwearable technology comprises a computer display projected onto the tile screen on the floor. Background music and game prompts are played simultaneously via an audio system, creating an immersive and interactive gaming experience. Cognitive-behavioral training based on VR technology comprised 4 steps (**Supplementary Table 2**) and 3 game scenarios (**Figure 2**). The training requires children to complete multiple tasks simultaneously, and utilizes an adaptive system that enables children to navigate between different scenarios. This process was designed to alleviate cognitive deficits in children. In scenes that combine both visual and aural stimuli, such as underwater worlds, country gophers, and aerial balloons, the perception of specific targets and the subsequent performance of post-perception motion tasks are performed simultaneously. In such scenarios, the child is required to respond to a specific target while ignoring distracting stimuli as they navigate an interactive ground screen to alter their position and engage with the intended target, while avoiding the unintended target. The procedures and images of the games in this intervention are presented in **Supplementary Figures 1** and **2**. The game’s difficulty is modified in real-time according to the child’s performance, thereby ensuring continuous and appropriate challenges at a preset difficulty level that is engaging yet manageable.

**Figure 2 f2:**
[figure not shown]
Overview of the three games in the Behavioral Training System for preschool children with ASD based on VR technology.

For each participant, a unique patient ID is generated, and the number of interventions will be recorded. Concurrently, the interactive ground screen collects real-time data on the children’s interactions, records scores, and analyses the children’s training indicators based on real-time CPT data. At the conclusion of each training session, the data will be transferred to a cloud-based data management platform, where it will be stored for later analysis. This will allow trainers to systematically and objectively customize training content.

#### Early family intervention

2.8.2

Early family intervention will adhere to the principles of child development. This intervention will entail a comprehensive assessment of each child and the formulation of an intervention program accordingly. The assessment will commence with an examination of each child’s neuropsychological development with the developmental characteristics of ASD. Subsequently, an assessment of the developmental level of children with ASD will be carried out across various domains. The assessment will further encompass an analysis of the family environment and all available resources. Based on the present analysis, an individualized education plan prioritizing social interaction as the core training content and utilizing games as the basic carrier will be formulated. Early family intervention will prioritize the family as the centre of intervention; as such, parents will be the primary implementers of the treatment, with therapists acting as supervisors. The therapist assumes the role of supervisor for the parents and oversees the implementation of the IEP at home. Parents will receive one hour of intervention training per week organized by the therapist. In addition, one hour of training per week will be conducted at home, in conjunction with the classroom video provided by the therapist. The intervention duration will be 12 weeks for each group. Weekly telephone and monthly outpatient follow-ups will be conducted to monitor the implementation of the parental intervention.

### Settings

2.9

The VR-technology-based intervention in the trial group will be implemented offline at each hospital, whereas the control group will undergo early home intervention after the parents are trained. Both groups will be required to undergo early home interventions guided by a rehabilitation team. A gradual approach to early family interventions will be provided by therapists (licensed psychologists and speech therapists) trained in performing early family interventions. These therapists will introduce concepts and strategies, demonstrate their use, and guide the parents in practicing them. The instructions provided by the therapist to each parent-child dyad will remain consistent throughout the study.

### Data management

2.10

The information obtained for this project will not be made available to any individual outside of the research team, with the exception of the investigators, to maintain confidentiality and personal safety. During the clinical trial and data processing phases, proper data management practices will be followed. All records, including original medical documents, protocol copies, patient identifiers, source data, informed consent forms, case report forms, and other relevant documents, will be accessible. Medical records and related forms must remain unaltered without proper authorization. Any necessary corrections should be made as additional statements with justification, and must be signed and dated by the physicians involved. The destruction of research documents from the clinical trials is not allowed.

### Risks and adverse events

2.11

Adverse events will be documented throughout the study, and an adverse event reporting system will be established following the guidelines set by the theoretical committee. In the case of serious adverse events, including death, life-threatening symptoms leading to hospitalization or prolonged hospitalization, congenital anomalies/deformities, and permanent or major disability, the investigator will be responsible for reporting the findings to the relevant ethics committee.

This study will concentrate on applying non-wearable VR technology and home-based interventions to enhance core symptoms in children with ASD. The planned intervention does not involve any invasive procedures, and will be delivered through an interactive floor screen or home intervention model, which are unlikely to cause any physical side effects. Additionally, the assessments planned to be used in this study are widely utilized in clinical settings, and are regarded as relatively low-risk owing to their non-invasive characteristics. Previous studies have indicated that cybersickness is a prevalent adverse reaction to VR experiences, manifesting as fatigue, discomfort, and dizziness (34). Prior to beginning the intervention, participants’ susceptibility to cybersickness will be assessed using the Motion Sickness Susceptibility Questionnaire Short Form. Results from this questionnaire will guide an individualized risk assessment to identify children who may have heightened sensitivity to VR-induced discomfort. For those participants without prior experience in VR, introductory exposure sessions will be provided to facilitate gradual adaptation at an individualized, comfortable pace. During the intervention sessions, a trained therapist will closely monitor each participant’s response, promptly adjusting, pausing, or discontinuing sessions if symptoms of discomfort or distress occur. Persistent adverse responses will lead to the child’s withdrawal from the intervention to prioritize their safety and well-being. Additionally, session duration and VR exposure time will be strictly controlled during the intervention and research assessments to prevent potential negative effects stemming from excessive or inappropriate VR usage.

## Statistical analysis

3

The fNIRS data will be analyzed using the NirSpark software package developed by HuiChuang in China. During preprocessing, the first 20 s of each recording will be removed to eliminate signal instability and ensure data quality. Motion artifacts will be identified and corrected on a per-channel basis using spline interpolation, and a band-pass filter (0.01–0.20 Hz) will be applied to reduce interference from general physiological noise. Optical density data will be converted to oxygenated hemoglobin (HbO2) concentration values based on the modified Beer–Lambert law, using age-adjusted differential path length factors of 5.5, 5.2, and 4.6 as appropriate (35). After preprocessing, a resting-state functional connectivity analysis will be conducted to examine connectivity between brain regions. The resting-state data for each subject and time point will be extracted, and the oxygenated hemoglobin levels in each brain region’s time series will be quantified. Pearson correlation coefficients will be calculated for oxygenated hemoglobin across channels and brain regions to assess connectivity. These coefficients, represented as r values, will be used as indices of whole-brain resting-state functional connectivity. To normalize the distribution, Fisher’s z-transformation will be applied to the correlation coefficients (r), producing transformed Z-values that represent the strength of connectivity for each channel. This should allow for comparisons of relative connectivity strength ROIs. Ultimately, focusing on the eight ROIs of the cerebral cortex, their resting-state functional connectivity intensities were analyzed in depth to reveal the functional interactions between different brain regions.

Data analyses will be performed using SPSS software (version 26; IBM Corp.). Paired-sample t-tests will be employed to assess for pre- and post-treatment comparisons between normally distributed measures. Similarly, the Kappa consistency test will be used to perform pre- and post-comparisons of count data. Independent sample t-tests will be employed for between-group comparisons of normally distributed measures, while nonparametric tests will be utilized for between- and within-group comparisons of non-normally distributed measures. Repeated ANOVAs will be conducted to evaluate the treatment effects within each group. The goal of this study is to identify any differences in variables between baseline and post-test measurements in both the treatment and control groups. The factors considered include time (before and after) and group (experimental vs. control), with each measure serving as a dependent variable. For measures that meet the normality test, means ± standard deviation will be used to describe results. Conversely, medians and percentiles will be employed for measures that do not meet the normality test. Count data will be presented as the median and interquartile range. Statistical significance will be defined as a p-value of 0.05 or less. To manage missing outcome data, we will assume that data are missing at random and will apply multiple imputation as the primary approach. Bonferroni correction adjustments will be applied where appropriate to control for the risk of Type I error due to multiple comparisons.

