### Randomization and blinding

2.5

Participants will be assigned randomly to either the experimental or control group in a 1:1 ratio, with randomization lists constructed by an independent statistician using SAS version 9.4 software. Group assignments were concealed using sequentially numbered, opaque, sealed envelopes prepared in advance. Upon enrollment, research staff opened the next envelope in the sequence to reveal the participant’s group assignment. Due to the nature of the intervention, blinding participants or therapists to group allocation was not feasible. However, to reduce assessment bias, all outcome evaluations will be conducted by independent assessors who are blinded to group assignments. To further ensure the reliability of outcome measurements, inter-rater reliability will be evaluated using intraclass correlation coefficients for clinician-administered observational tools such as the ADOS-2 and CARS. The results of the trial, including the patient’s identifying information and details of the intervention, will be de-identified. Final analyses will be performed by a statistician who remains blinded to group allocation.

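### The Kappa test is assigned to pre-post comparison of count data, but it measures agreement and cannot show change

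*Protocol article*

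**What the plan says.** Section 3 (Statistical analysis) first deals with continuous measures: "Paired-sample t-tests will be employed to assess for pre- and post-treatment comparisons between normally distributed measures". The next sentence reads: "Similarly, the Kappa consistency test will be used to perform pre- and post-comparisons of count data". The same section gives the purpose: "The goal of this study is to identify any differences in variables between baseline and post-test measurements in both the treatment and control groups". It sets the threshold: "Statistical significance will be defined as a p-value of 0.05 or less". It also says how such data are to be summarised: "Count data will be presented as the median and interquartile range".

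Agreement between raters, the usual use of Kappa, is handled elsewhere. Section 2.5 (Randomization and blinding) states: "inter-rater reliability will be evaluated using intraclass correlation coefficients for clinician-administered observational tools such as the ADOS-2 and CARS".

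For the comparison of the arms, Section 3 says: "Independent sample t-tests will be employed for between-group comparisons of normally distributed measures", with nonparametric tests where normality fails.

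**The concern.** The Kappa sentence is joined to the paired t-test as its counterpart, and the declared aim is to find differences between baseline and post-test. Kappa is therefore being used as a test of change. It cannot be a rater-agreement check that strayed into the wrong place, because Section 2.5 gives that task to intraclass correlation coefficients.

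The null hypothesis of the Kappa test is that the baseline and post-treatment classifications agree only as often as chance would produce. Rejecting it with a positive kappa says that children tended to stay where they were. Change in a paired categorical variable is a shift in the margins, which McNemar's test (two categories) or a marginal homogeneity test (ordered categories) examines.

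An analyst who followed the sentence could report a small p-value as a pre-post effect when the table shows stability, and could miss a large improvement.

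**Working it through.** The plan gives no figure for this point, so there is none to reproduce. The check compares what the two tests return on the same pre/post tables.

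**Inputs.** Arm size 80 (Section 2.2, Sample size calculation). Threshold 0.05 (Section 3). The baseline split of 50 severe and 30 not severe is an assumption, because the article gives none.

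**Formulas.** With cell proportions from the pre/post table, row margins r and column margins c:
- observed agreement po = sum of the diagonal; chance agreement pe = Σ r·c
- kappa = (po − pe)/(1 − pe)
- variance under kappa = 0: [pe + pe² − Σ r·c·(r + c)] / [n(1 − pe)²]; z = kappa/SE, two-sided p
- exact McNemar: two-sided binomial test of the improvers against the worseners; when b improve and none worsen, p = 2 × 0.5^b

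**Worked case: 45 of 50 improve, none worsen.**
- Margins: rows 0.625 and 0.375; columns 5/80 = 0.0625 and 75/80 = 0.9375.
- po = 35/80 = 0.4375.
- pe = 0.625 × 0.0625 + 0.375 × 0.9375 = 0.3906.
- kappa = 0.0469/0.6094 = 0.077.
- Σ r·c·(r + c) = 0.4883, so variance = (0.3906 + 0.1526 − 0.4883)/(80 × 0.3713) = 0.00185 and SE = 0.0430.
- z = 1.79, p = 0.07.
- McNemar: 2 × 0.5^45 = 5.7e-14.

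**Range of outcomes, binary measure, n = 80, 50 severe at baseline.**

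| Pre to post | kappa | Kappa p | Exact McNemar p |
|---|---|---|---|
| Nobody changes | 1.00 | 3.7e-19 | 1 |
| 5 improve, 5 worsen | 0.73 | 5.4e-11 | 1 |
| 25 of 50 improve, none worsen | 0.43 | 3.0e-6 | 6.0e-8 |
| 40 of 50 improve, none worsen | 0.16 | 0.009 | 1.8e-12 |
| 45 of 50 improve, none worsen | 0.08 | 0.07 | 5.7e-14 |
| All 50 improve, none worsen | 0.00 | none (null variance 0) | 1.8e-15 |

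From no change to complete improvement, the Kappa p-value rises while the McNemar p-value falls.

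**Sensitivity to the assumed split.** With 40 severe and 40 not severe, the pattern is the same. Nobody changes: kappa 1.00, p = 3.7e-19. 36 of 40 improve: kappa 0.10, p = 0.040 (McNemar 2.9e-11). All 40 improve: kappa 0, no p-value (McNemar 1.8e-12).

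**Three categories.** Section 2.7.3 gives CARS bands with cut-offs at 30 and 36. Suppose 30 children move from severe to mild-moderate and 50 from mild-moderate to below 30. Then po = 0, and pe = 0.625 × 0.375 = 0.2344, because only the middle band is occupied at both times. So kappa = −0.2344/0.7656 = −0.31, SE 0.0342, z = −8.94, p = 3.7e-19. If the same 80 children all stay put, kappa is 1.00 with the same p = 3.7e-19. The p-value does not separate the two cases.

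**The case against.** The strongest reply is about reach. No endpoint named in the article depends on this sentence. The sample size rests on the ADOS score; ABC, CARS, SDQ and ADOS-2 are scored scales; the fNIRS connectivity measures are Fisher z-values. Section 3 provides t-tests, nonparametric tests and repeated ANOVA for such data. The CARS bands appear as a guide to reading the score, and the article does not say that the band will be analysed. The Kappa test is also a within-arm test, so it leaves the randomised comparison of the scales untouched. All of this stands.

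A second reply is that the reversal is not universal. That also stands. The pattern in the table needs a binary measure with both categories present at baseline. If every child starts in one category and none moves, kappa is undefined. With three bands, everyone improving by one band gives a very small p. A reader might infer that no change always gives the strongest p-value and universal improvement never gives one; that is too general.

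A third reply is that a strong shift loses significance only in the degenerate case where everyone ends in one category. This does not stand: 45 of 50 improving, with five children still severe, already gives p = 0.07.

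A reader might also object that no between-arm test is named for categorical data. An article may leave that to the analysis plan, so it is no part of this point. The same allowance does not cover the Kappa sentence, which positively names a test for a purpose it cannot serve.

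**Conclusion.** The sentence is wrong as written. Kappa tests agreement beyond chance, and its p-value cannot be read as evidence of a pre-post difference. In the assumed binary example it is about 4e-19 when nobody changes and about 0.07 when 45 of 50 improve. With three or more categories, a small p can mean stability or universal movement.

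The figures rest on an assumed baseline split; the argument itself rests only on what the test's null hypothesis is. Treating count data as categorical is also an interpretation. The median and interquartile range summary in the same section points towards true counts, and the article does not settle which is meant. Kappa tests change in neither.

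A reader might infer that the primary result, or every categorical conclusion, is reversed. The document does not support that: it declares no categorical endpoint, and the primary ADOS-2 score has other tests. This is a correction of limited impact.

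**What to change.** In Section 3, replace the Kappa sentence with a paired test of change and say what count data means:

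- binary measures: McNemar's test;
- ordered categories: a marginal homogeneity test;
- true counts: the Wilcoxon signed-rank test.

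Bring the summary statistic into line with that choice, since median and interquartile range do not suit unordered categories. Label the paired test as a within-arm description, and state that any claim of a treatment effect rests on the between-arm comparison.

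The cost is one replaced sentence and a clarified definition, carried into the analysis plan if one exists. No new data are needed. Section 2.4 (Trial status) gives the trial as recruiting, with an anticipated end of 30 September 2026; the change should be made before the data are analysed.

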### Sample size calculation

2.2

The sample size was determined based on the primary outcome measure and the scores from the ADOS scale. Previous studies reported an average ADOS-2 score of 16.9 ± 4.1 for children with ASD (25). In this study, we hypothesized a clinically meaningful difference of 2 points in the intervention group compared to the control group, indicating the efficacy of the VR-based intervention. The required sample size was calculated using the PASS 15.0 software, with the stipulation of α=0.05 and the test efficacy 1-β=0.8. This process yielded a sample size of 72 patients. Given a 10% loss of visits, the calculated sample size for each group was 80, with a total sample size of 160 cases.

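### The Kappa test named for before-and-after comparison of count data measures agreement, so its p-value does not show whether anything changed; the summary given for count data does not fit it either

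*Protocol article*

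**What the plan says.** The Statistical analysis section of the protocol article assigns tests by type of data. For continuous measures that pass a normality check, "Paired-sample t-tests will be employed to assess for pre- and post-treatment comparisons between normally distributed measures". The next sentence opens with a word that draws a parallel and then states that "the Kappa consistency test will be used to perform pre- and post-comparisons of count data". Nonparametric tests are reserved for measures that are not normally distributed, which the section treats as a class separate from count data. The purpose is stated there too: "The goal of this study is to identify any differences in variables between baseline and post-test measurements in both the treatment and control groups". On description, "Count data will be presented as the median and interquartile range". The threshold is also given: "Statistical significance will be defined as a p-value of 0.05 or less".

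Kappa is not named for rater reliability. Under Randomization and blinding (section 2.5), "inter-rater reliability will be evaluated using intraclass correlation coefficients for clinician-administered observational tools such as the ADOS-2 and CARS".

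**The concern.** A before-and-after comparison of a classification asks whether the proportion in each category moved, which is a question of marginal homogeneity. Kappa asks whether the two classifications of the same child agree more than chance would produce, and its null hypothesis is no agreement beyond chance. Children who stay where they were produce high agreement and a small p-value. Children who move can produce agreement no better than chance and a large one. Read against the section's 0.05 threshold as a test of change, a stable arm would be called significant and a strongly improving arm could be called null.

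The wording closes off the benign readings. The parallel with the paired t-test gives Kappa the job of detecting change, the stated goal is to find differences, and rater agreement is already handled by another statistic.

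The descriptive sentence adds a second difficulty. If count data means categories, a median and interquartile range do not describe a binary or nominal classification. If it means numeric counts, the summary is reasonable but Kappa fits even less well. Under neither reading do the two sentences work together.

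**Working it through.** No figure in the protocol depends on Kappa, so there is nothing to reproduce. The check is whether the p-value reported with kappa follows change in constructed paired tables.

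**Inputs.** The table size of 72 is the evaluable number per arm implied by Sample size calculation (section 2.2): 72/(1 − 0.10) = 80, and "the calculated sample size for each group was 80, with a total sample size of 160 cases". All cell counts are assumptions, because the protocol gives no categorical before-and-after data. Cells are listed as (above cut-off at both times, before only, after only, neither).

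**Formulas.**
- Observed agreement po = (both + neither)/n. Expected agreement pe = sum over categories of r × c, where r and c are the before and after proportions.
- kappa = (po − pe)/(1 − pe).
- Null standard error = √[pe + pe² − Σ r c (r + c)] / [(1 − pe)√n]; z = kappa divided by this.
- Exact McNemar: two-sided binomial test, probability 0.5, on the children who changed category.

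**Table A, nobody changes: (40, 0, 0, 32).**
- po = 72/72 = 1. pe = (40² + 32²)/72² = 2624/5184 = 0.506. kappa = 1.0.
- Σ r c (r + c) = 2 × (0.5556³ + 0.4444³) = 0.5185. The root is √(0.5062 + 0.2562 − 0.5185) = 0.494, which equals 1 − pe, so the standard error is 1/√72 = 0.118 and z = √72 = 8.49, p about 2 × 10⁻¹⁷.
- McNemar: no child changed, p = 1.

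**Table B, large improvement: (18, 36, 6, 12).**
- Above the cut-off before: 18 + 36 = 54. After: 18 + 6 = 24.
- po = 30/72 = 0.4167. pe = (54 × 24 + 18 × 48)/72² = 2160/5184 = 0.4167. kappa = 0, z = 0, p = 1.
- McNemar, 36 against 6: 2 × P(X ≤ 6), X binomial (42, 0.5), = 2 × 6,220,768/2⁴² = 2.8 × 10⁻⁶.

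**Two further tables mark the limits of the claim.**
- Table C, one-way improvement with n = 80: (30, 30, 0, 20). po = 50/80 = 0.625. pe = 0.75 × 0.375 + 0.25 × 0.625 = 0.4375. kappa = 0.1875/0.5625 = 0.33, z = 4.0, p about 6 × 10⁻⁵. McNemar on 30 against 0 gives 2 × 0.5³⁰ = 1.9 × 10⁻⁹. Both are significant, but Kappa only because of residual agreement.
- Table D, all 72 above at baseline and 40 improve: (32, 40, 0, 0). kappa = 0 with a null standard error of zero, so no p-value exists. McNemar on 40 against 0 gives about 2 × 10⁻¹².

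| Table | Real change | p with kappa | Exact McNemar p |
|---|---|---|---|
| A | none | about 2 × 10⁻¹⁷ | 1 |
| B | 54/72 to 24/72 | 1 | 2.8 × 10⁻⁶ |
| C | 60/80 to 30/80 | about 6 × 10⁻⁵ | 1.9 × 10⁻⁹ |
| D | 72/72 to 32/72 | undefined | about 2 × 10⁻¹² |

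**The case against.** The strongest reply is about reach. The protocol names no categorical before-and-after endpoint. The outcome behind the sample size is the ADOS-2 score; the ABC, CARS and SDQ are described as scored scales; and the fNIRS results are transformed correlations. The CARS severity bands (section 2.7.3) and the ABC cut-off of 62 (section 2.7.2) appear in the descriptions of the instruments and not as endpoints. This stands, and it keeps the point to supporting analyses.

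Three stronger inferences are tempting, and the document does not support them.
- A reader might infer that the efficacy conclusion is compromised. Between-group comparisons are given to independent t-tests or nonparametric tests, so the Kappa sentence does not bear on the ADOS-2 comparison.
- A reader might infer that Kappa will usually point the wrong way. Table B was built so that before and after status are exactly independent, which forces kappa to zero; nothing shows this pattern to be typical, and in Table C both tests are significant. What can be said is that Kappa's p-value is not informative about change.
- A reader might infer that categorical outcomes have no between-arm test. A condensed article may leave that to an analysis plan that is not shown, and the nonparametric provision could cover ordered bands.

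It is also fair to say that count data need not mean categorical data. That ambiguity changes which replacement test is right. It does not make Kappa suitable.

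**Conclusion.** The test is wrong as written for the purpose the section gives it, and the sentence on describing count data does not fit with it. With assumed cell counts and 72 children, Kappa is highly significant when nothing changes (Table A) and gives p = 1 when the share above a cut-off falls by 30/72, about 42 percentage points (Table B). The tables assume a binary classification and the usual test of kappa against zero; they show what can happen and do not forecast this trial's data.

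The consequence is confined to supporting within-arm analyses of count data, for example CARS bands or the ABC cut-off if they are analysed that way. The point should be fixed, but it does not threaten the main comparison.

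**What to change.** In the Statistical analysis section:

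1. State whether count data means categories or numeric counts, and name the variables concerned.
2. For categories, replace Kappa with McNemar's test (binary) or a marginal-homogeneity or signed-rank test (ordered bands), and report n (%) in place of the median and interquartile range.
3. For numeric counts, replace Kappa with a paired test of change such as the signed-rank test, and keep the median and interquartile range.

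The cost is the rewording of two sentences and one added definition. No data collection, sample size or ADOS-2 analysis changes. Trial status (section 2.4) reports that recruitment is under way, so making the correction before analysis avoids having to justify a change of test after the results are seen.
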